### Substudy 2: Correlates of CGM Adherence: Cross-Sectional Mixed Methods Study

#### Design and Population

Substudy 2 is a cross-sectional mixed methods study using supervised face-to-face interviews with adolescents aged 10-18 years drawn from substudy 1. RMs will randomly sample participants from the Al Shifa–derived cohort. The dependent variable, pattern of CGM use, will be dichotomized as CGM optimizers (≥6 days/week) and CGM subusers (<6 days/week or discontinued), consistent with prior pediatric work [25].

Eligible participants will include children aged 10-18 years with T1DM who received CGM under the national initiative and whose primary caregiver consents. Children will be excluded if they are unable to complete the structured interview owing to severe cognitive or sensory impairment.

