**Objective:**

This multiphase translational research project aims to (1) characterize the population of Omani children with T1DM; (2) identify demographic, psychosocial, dietary, and physical activity correlates of optimal CGM use; (3) develop, train, and validate an AI-assisted behavioral predictive tool “OMNIdiasense” to forecast CGM adherence prior to device dispensing; and (4) pilot test the OMNIdiasense tool.

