### Substudy 1: Characteristics and Glycemic Outcomes of Omani Children Receiving CGMs

#### Design and Population

Substudy 1 is a retrospective cohort analysis of all Omani children with T1DM who received CGM through the national rollout between July 2024 and February 2025 across the 11 governorates. The minimum analytic exposure window is 3 months of CGM use from baseline.

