#### Handling of Missing Data, Class Imbalance, Overfitting, and Feature Selection

Missingness will be quantified by variable and pattern. Variables with >40% missingness will be excluded unless they carry strong prior clinical value, in which case they will be retained with an explicit missing indicator. Item-level missing data on validated scales will be imputed using each scale’s published rules; remaining missingness will be addressed by multiple imputation by chained equations (m=20) under a missing-at-random assumption, with a tipping-point sensitivity analysis to test robustness against a missing-not-at-random scenario.

Class imbalance between optimizers and subusers will be addressed at 2 levels: stratified sampling during cross-validation to preserve outcome proportions in every fold, and class-weighted loss functions (inverse-frequency weights) for the gradient-boosted, SVM, and neural-network classifiers. Synthetic minority oversampling will be evaluated as a sensitivity analysis only and not as the primary approach, to avoid optimistic generalization.

Overfitting will be controlled through nested cross-validation (outer 5-fold for performance estimation, inner 5-fold for hyperparameter tuning), L1/L2 regularization for linear models, early stopping and shrinkage for boosted trees, and dropout and weight decay for the neural network. The full train-test partition (80/20) will be temporally separated where possible (children enrolled later become the held-out set) to give a more realistic estimate of prospective performance.

Feature selection will use a stability-selection wrapper around L1-penalised logistic regression with 100 subsampled fits; features selected in ≥60% of subsamples will be retained, in addition to a clinically prespecified core set (age, sex, diabetes duration, baseline HbA_1c_, insulin modality, governorate, BenCGM, BurCGM, SEDM, and PAID-Peds). The final model will be sparse and interpretable; Shapley additive explanations (SHAP) values will be reported to support clinical interpretation of individual predictions.

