#### Inclusion and Exclusion Criteria

Quasi-experimental component: existing children with T1DM aged 10-18 years classified as CGM subusers in substudy 2; primary caregiver consents and child assents.

RCT component: newly diagnosed children with T1DM, aged 10-18 years, eligible for CGM under the national program, who have not yet received CGM. Exclusion: severe psychiatric or cognitive comorbidity precluding informed assent or interview participation.

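### The pre-dispensing model is forced to use psychosocial scores measured about 16 months or more after CGM receipt, so reverse causation cannot be excluded and internal validation cannot detect it

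*Protocol article*

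**What the plan says.** **Intended use.** The Abstract (Objective) gives the tool's purpose as "to forecast CGM adherence prior to device dispensing". Comparison With Prior Work presents prediction ahead of dispensing as one of the project's distinguishing features. In Substudy 3 (Design), the RCT intervention arm is assessed before CGM starts. Inclusion and Exclusion Criteria define the RCT children as newly diagnosed, "eligible for CGM under the national program, who have not yet received CGM".

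**Source of the psychosocial inputs.** Substudy 1 (Design and Population) covers children who "received CGM through the national rollout between July 2024 and February 2025", and adds: "The minimum analytic exposure window is 3 months of CGM use from baseline". The next Design and Population section states: "Substudy 2 is a cross-sectional mixed methods study". It uses "interviews with adolescents aged 10-18 years drawn from substudy 1". Eligibility is limited to "children aged 10-18 years with T1DM who received CGM under the national initiative". At interview each child is classed as an optimizer or a subuser, and subusers include those who have stopped. The Results section plans full Substudy 2 recruitment from June 2026.

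**How the inputs enter the model.** The section on missing data, class imbalance, overfitting and feature selection keeps a core set whatever the stability selection finds. That set ends with "insulin modality, governorate, BenCGM, BurCGM, SEDM, and PAID-Peds". AI Model Development also lets Substudy 2 effect sizes guide the remaining candidate features.

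**Validation.** Performance is estimated by nested cross-validation and a 20% hold-out, split by time where possible. Recalibration is done within the same folds. External Validation adds a prospective cohort enrolled at least 3 months after model lock and a two-site replication using the same forms. For neither does it say that predictors are taken before the device is dispensed.

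**The concern.** A model used before dispensing needs predictors as they stand before dispensing. Perceived benefit and burden of a sensor are the inputs most open to change through wearing it or giving it up. Self-efficacy and diabetes distress may move too, though they are not specific to CGM. In the training data all four are recorded after that experience, alongside or after the outcome label.

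If part of the optimizer–subuser gap in these scores arose after wear began, the fitted weights rest partly on information that a CGM-naive child does not yet carry. The same scores are used for fitting, tuning, hold-out testing and recalibration, so a good internal result would say nothing about this.

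At stake are the performance claims for the project's central product and the risk category discussed with intervention-arm families. The section on fairness treats the false-negative rate as the most consequential error. That rate would also be estimated on inputs taken at the wrong time.

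**Working it through.** The plan states no figure for this, so there is none to reproduce. The check has four steps.

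**1. Time from CGM receipt to interview**

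| CGM received | Interviews start | Gap |
|---|---|---|
| July 2024 (earliest) | June 2026 | 23 months |
| February 2025 (latest) | June 2026 | 16 months |

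The gap is therefore at least about 16 months for every child, and longer for those interviewed later.

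**2. Can the planned validation see the problem?**

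| Layer | Scores used | Can it detect the problem? |
|---|---|---|
| Nested cross-validation | Substudy 2, after wear | No |
| 20% hold-out, even if split by enrolment date | Substudy 2, after wear | No |
| Isotonic or Platt recalibration | Same folds | No |
| Prospective temporal cohort | Timing relative to dispensing not stated | Only if taken before dispensing |
| Two-site replication | Same forms; timing not stated | Only if taken before dispensing |

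The temporal cohort may also report too late to inform the RCT. Feature engineering is scheduled for the third quarter of 2026 and pilot recruitment for the fourth. No lock date is given. If lock came at the end of September 2026 (assumption), temporal enrolment could start no earlier than the end of December 2026.

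**3. Illustration for one scale**

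Assume normal scores with equal variance and a standardized optimizer–subuser difference d = 0.8 at interview. Then AUROC = Φ(d/√2). The value of d and the shares below are assumptions, not protocol figures.

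| Share of the gap arising after wear | d before CGM | AUROC before CGM |
|---|---|---|
| None | 0.8 | Φ(0.566) = 0.71 |
| Half | 0.4 | Φ(0.283) = 0.61 |
| All | 0 | Φ(0) = 0.50 |

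**4. Simulation with calibration**

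A pre-CGM score X0 is standard normal. Wear Y is logistic in X0 with slope b, with 50% optimizers. The interview score is X1 = X0 + g·Y. A logistic model is fitted on X1 and applied to X0. Triplets are for b = 0 / 0.25 / 0.5.

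| g (SD) | AUROC at interview | AUROC before CGM | Calibration slope before CGM |
|---|---|---|---|
| 0 | 0.50 / 0.57 / 0.64 | 0.50 / 0.57 / 0.64 | not estimable / 1.00 / 1.00 |
| 0.5 | 0.64 / 0.70 / 0.76 | 0.50 / 0.57 / 0.64 | about 0 / 0.33 / 0.49 |
| 1.0 | 0.76 / 0.81 / 0.86 | 0.50 / 0.57 / 0.63 | about 0 / 0.20 / 0.32 |

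With g at 0.5 or 1.0, the mean predicted optimizer probability is 0.37 to 0.47 against 0.50 observed. If stopping lowers subusers' scores instead of wear raising optimizers' scores, symmetry gives 1 − 0.47 = 0.53 to 1 − 0.37 = 0.63. The direction of miscalibration is therefore unknown as well. With g = 0 nothing is lost. A single cross-sectional interview cannot show which row applies.

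**The case against.** The timing facts are not in dispute, but several stronger readings are tempting and go too far.

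- **That the model learns the consequences of wear, or that leakage is established.** A reader might infer this from the sequence of events. The Substudy 2 Conceptual Framework assumes the opposite direction, with attitudes shaping use, and cross-sectional data cannot decide between the two. The documents support only that reverse causation cannot be excluded.
- **That a CGM-naive child cannot answer BenCGM or BurCGM in an equivalent way.** This depends on item wording and any adaptation in Multimedia Appendix 4, which is not shown.
- **That the whole tool is compromised.** Age, sex and governorate are unaffected, and Substudy 1 (Data Collection) holds pre-CGM HbA1c, anthropometric, laboratory and treatment data. The one-scale illustration does not estimate the loss for the full model.
- **That all of Substudy 3 is affected.** The 100 single-arm children have used CGM. Within Substudy 3, CGM-naive use of the tool means the 25 RCT intervention children.
- **That the RCT result is biased.** Allocation is randomized, and the Intervention section gives every intervention-arm child three MI consultations whatever the score. A poor score weakens tailoring but does not bias the between-group difference in wear.

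The plan also limits harm. The score cannot restrict CGM access, families are told that it is a research-stage estimate, and any later implementation requires satisfactory external validation. All of this stands. It narrows the point, but it does not supply pre-dispensing predictors for a model that claims to predict before dispensing.

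There is also a fair argument against removing every psychosocial scale. Identifying such correlates and building them into the tool are stated objectives, and SEDM and PAID-Peds can be asked before dispensing.

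**Conclusion.** The point holds as a mismatch between when the forced psychosocial predictors are measured and when the model is to be used. The gap from device receipt to measurement is about 16 months or more, and every internal validation layer shares it. Reported discrimination and calibration may therefore be optimistic for CGM-naive children.

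The size is unknown. For one scale under the assumed 0.8 SD difference, the range runs from no loss (AUROC 0.71) to no information (0.50). The timing is certain from the text, but the mechanism is not.

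The consequence falls on the tool's pre-dispensing performance claims, the guidance given in the RCT intervention arm, and later pre-dispensing use. As of April 2026 full Substudy 2 recruitment and model building were still ahead, so the change can be made in time.

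**What to change.** 1. **Feature selection section.** For the version used before dispensing, remove BenCGM and BurCGM from the mandatory core set. Stability selection should not bring them back into that version until item 3 is met.
2. **Model reporting.** Give discrimination, calibration and false-negative rate with and without all interview-time scales. Use the model built only on pre-CGM data (demographics, diabetes history, and pre-CGM clinical and treatment values from Substudy 1) as the reference for CGM-naive use, with feature selection rerun on those predictors.
3. **External Validation.** State that predictors in the temporal-validation cohort are collected before dispensing, with later wear as the outcome. Make any claim of pre-dispensing performance conditional on that result. The same condition applies to keeping SEDM, PAID-Peds or expectation-type items in the pre-dispensing version.
4. **Strengths and Limitations.** State that the training scores were taken after CGM experience and that reverse causation cannot be excluded.

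The cost is wording in these sections, one extra model fit, and fixing the time of predictor collection in a cohort that is already planned. The stated AUROC for pre-dispensing use will probably be lower. The psychosocial work is kept: the scales stay in Substudy 2 and can re-enter the pre-dispensing version once measured at the right time.

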#### Conceptual Framework

Despite CGM’s technical maturity, the majority of adolescents with T1DM do not meet glycemic targets [20-24]. Self-management decisions are shaped by perceived benefit and burden of CGM, self-efficacy, coping responses, diabetes distress, dietary patterns, and physical activity [25,27]. Substudy 2 measures these constructs and their open-ended elaborations to inform feature selection for OMNIdiasense.

#### Expected Outcomes

Primary outcomes of substudy 2 are the standardized mean differences and odds ratios for each psychosocial and behavioral instrument (Benefits of Continuous Glucose Monitoring Scale [BenCGM], Burden of Continuous Glucose Monitoring Scale [BurCGM], Response to Stress Questionnaire-Pediatric Diabetes [RSQ-PD] coping factors, Self-Efficacy for Diabetes Management Scale [SEDM], Problem Areas in Diabetes-Pediatric version [PAID-Peds], Physical Activity Questionnaire for Adolescents [PAQ-A], and dietary screener) between optimizers and subusers. Secondary outcomes are the qualitative themes generated from open-ended responses, the convergent mixed methods joint display, and the ranked feature list passed to substudy 3 for model training (Multimedia Appendix 3).

#### Sample Size

Assuming an optimizer prevalence of approximately 50% [25] and aiming to detect medium-effect-size predictors in a multivariable logistic model with up to 8 predictors, a minimum of 240 participants will provide sufficient statistical power (≥10 events per variable). Recruitment will be stratified across the 11 governorates proportional to CGM dispensations.

#### Measurements

The face-to-face interview will include the following components, administered in Arabic where validated translations are available (Multimedia Appendix 4). Questionnaires that require official approval from the original authors or involve payment or restricted use will be obtained accordingly. Components of the questionnaire include the following:

Demographics and diabetes management: age, gender, region, current insulin modality (multiple daily injections vs insulin pump), past or current CGM use, duration of CGM use; diabetes duration imported from substudy 1.BenCGM and BurCGM: 8-item Likert scales each, validated in adolescents aged 12-19 years [25,35]. Cronbach α will be reestimated in a pilot phase.RSQ-PD: 57-item adolescent-specific measure yielding 5 proportional coping/stress factors [36-38].SEDM: 10-item single-factor scale validated in T1DM adolescents 13-17 years [39,40].PAID-Peds: 20-item measure of diabetes distress in youth [41].PAQ-A, Arabic version [42].Short dietary history screener [43].Open-ended items: compliance with CGM, school and educational performance, barriers and facilitators, side effects, and recommendations.

#### Data Analysis

Quantitative analyses will compare optimizers and subusers using chi-square tests, *t* tests, and Mann-Whitney *U* tests, with multivariable logistic regression to identify independent psychosocial and behavioral predictors of optimal CGM use. Qualitative responses to open-ended items will be audio-recorded with consent, transcribed verbatim, and analyzed in NVivo (Lumivero) by 2 independent coders (1 bilingual Arabic-English nurse researcher and 1 public health researcher) using a hybrid inductive-deductive approach; discrepancies will be resolved by a third senior coder, and a 20% subsample will be member-checked for accuracy. Field notes will be written within 24 hours of each interview. Findings will be triangulated using a convergent mixed methods design with joint displays. Reporting will follow STROBE (Multimedia Appendix 2) for the quantitative component and COREQ (Consolidated Criteria for Reporting Qualitative Research; Multimedia Appendix 5) for the qualitative component.

### Substudy 3: Pilot Evaluation of OMNIdiasense

#### Design

Substudy 3 evaluates the AI-assisted assessment tool OMNIdiasense through 2 parallel components, both fed by an embedded AI model-development workstream described below.

Quasi-experimental single-arm pilot: 100 existing CGM subusers identified in substudy 2 receive OMNIdiasense assessment prior to CGM reintroduction, followed by MI-guided behavioral support delivered by a trained diabetic nurse within the routine pediatrics endocrine clinics.Pilot RCT: 50 newly recruited children with T1DM, randomized 1:1 to (1) intervention, OMNIdiasense assessment plus MI-guided support before CGM initiation or (2) usual care without exposure to the tool. Both arms receive CGM and standard clinical follow-up.

All 150 participants are followed for 12 months, with assessments at baseline, 3, 6, and 12 months. The flow of participants is presented in Figure 1.

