**Figure 1 figure1:**
[figure not shown]
Multiphase study flow of the OMNIdiasense project. AUROC: area under the receiver operating characteristic curve; BenCGM: Benefits of Continuous Glucose Monitoring Scale; BP: blood pressure; BurCGM: Burden of Continuous Glucose Monitoring Scale; CGM: continuous glucose monitoring; HbA1c: hemoglobin A1c; HIS: health information system; LFT: liver function test; MoH: Ministry of Health; NN: neural network; PAID: Problem Areas in Diabetes; PAQ-A: Physical Activity Questionnaire for Adolescents; RFT: renal function test; RSQ: Response to Stress Questionnaire;
SEDM: Self-Efficacy for Diabetes Management Scale; SQU: Sultan Qaboos University; SVM: support vector machine; T1DM: type 1 diabetes mellitus; TRIPOD+AI: Transparent Reporting of a Multivariable Prediction Model for Individual Prognosis or Diagnosis + Artificial Intelligence.

**Table 1 table1:** Description of the substudies by design, outcomes, and how each informs the next.

Substudy and aim	Design	Primary outputs/outcomes	How it informs the next phase
Substudy 1: characterize population	Retrospective cohort (Al Shifa records, n~1500)	Population characterization; pre/post HbA_1c_^a^, anthropometrics, BP^b^, lipids, RFT^c^, LFT^d^; sensor-wear days per week; baseline adherence prevalence	Provides the deidentified structured dataset (clinical + adherence label) used as the supervised-learning input for OMNIdiasense; defines candidate clinical predictors.
Substudy 2: identify correlates	Cross-sectional mixed methods (n=240 face-to-face interviews + qualitative open-ended responses)	Quantitative effect sizes for BenCGM^e^, BurCGM^f^, RSQ^g^, SEDM^h^, PAID-Peds^i^, PAQ-A^j^, and dietary screener on optimizer vs subuser status; qualitative themes on barriers and facilitators	Provides the psychosocial and behavioral feature set, the qualitative themes that inform MI content, and the effect sizes used to prioritize features for the AI model.
Substudy 3: AI tool development (7-step pipeline with validation hierarchy)	Prediction model development on combined substudy 1 + 2 dataset	OMNIdiasense risk score (probability of subuser status), with discrimination, calibration, and fairness metrics	The validated model becomes the assessment tool tested in the 2 evaluation arms below.

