#### AI Model Development (OMNIdiasense)

The AI tool will be codeveloped by the MoH digital-health team and computer scientists from Sultan Qaboos University. The development pipeline comprises 7 steps, expanded below to address missing data, class imbalance, overfitting, feature selection, calibration, fairness, and external validation.

Data preparation: integration and cleaning of deidentified data from substudies 1 and 2 (demographic, clinical, laboratory, anthropometric, psychosocial, and behavioral).Feature engineering: selection of candidate predictors informed by substudy 2 effect sizes and clinical face validity.Model selection and training: comparison of supervised classifiers (logistic regression, gradient-boosted trees, support vector machines, and a small feed-forward neural network) using stratified cross-validation; evaluation by area under the receiver operating characteristic curve, sensitivity, specificity, calibration, and net reclassification improvement.Behavioral pattern recognition: unsupervised clustering of lifestyle and dietary data to derive interpretable phenotypes used for personalized recommendations.Initial testing: internal validation on a held-out 20% partition.Optimization: iterative refinement on the basis of clinician and family feedback.Deployment: secure web-based interface integrated into the diabetes clinic workflow with role-based access and audit logging.

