## Discussion

### Anticipated Principal Findings

We anticipate 3 principal findings. First, substudy 1 is expected to show that pediatric CGM uptake in Oman is high in the first 6 months of dispensing, but that a clinically important minority becomes subusers by month 3, with measurable variation across governorates. Second, substudy 2 is expected to confirm prior international findings that perceived benefit and burden of CGM, self-efficacy, and diabetes distress are the strongest psychosocial correlates of optimizer status, with additional Omani-specific contributors emerging from the open-ended responses. Third, substudy 3 is expected to show that OMNIdiasense, used as a decision-support adjunct followed by MI-guided behavioral sessions, is feasible to deliver, acceptable to families and clinicians, and produces a clinically meaningful between-group difference in adherence at 12 months that can power a future definitive trial.

These anticipated findings are framed as testable hypotheses, not foregone conclusions, and all statements throughout the abstract, manuscript, and conclusion have been rechecked to ensure that the strength of language matches the strength of inference that the proposed methodology can support.

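### The single-arm pilot's n=100 must come from substudy 2's 240 interviewees, with no allowance for refusal, and these children are also in the model development data

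*Protocol article*

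**What the plan says.** The Design section of substudy 3 takes "100 existing CGM subusers identified in substudy 2 receive OMNIdiasense assessment prior to CGM reintroduction". The Inclusion and Exclusion Criteria make this the entry rule: "existing children with T1DM aged 10-18 years classified as CGM subusers in substudy 2; primary caregiver consents and child assents". No second source is named.

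Table 1 describes substudy 2 as "Cross-sectional mixed methods (n=240 face-to-face interviews + qualitative open-ended responses". Its Sample Size section begins "Assuming an optimizer prevalence of approximately 50% [25" and concludes that "a minimum of 240 participants will provide sufficient statistical power (≥10 events per variable". Children are drawn at random from the Al Shifa cohort, in proportion to dispensations by governorate. Nothing in the article oversamples subusers.

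The substudy 3 Sample Size section says that the 100 are powered for paired change in adherence and HbA1c. It gives no effect size, SD or dropout allowance for that component.

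Under Anticipated Principal Findings the protocol expects that "a clinically important minority becomes subusers by month 3".

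The first step of model development is "integration and cleaning of deidentified data from substudies 1 and 2", with an 80/20 split into training and held-out parts. The Outcomes section lists change in the OMNIdiasense risk score as a key secondary outcome. Table 2 names the score as the tool for optimizer or subuser status at baseline, 3, 6 and 12 months.

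**The concern.** There are two separate problems.

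The first is supply. Substudy 2 was sized for a regression, not as a recruitment pool. A closed pool of 240 must supply 100 children of one outcome class who also agree to a 12-month study with three consultations. If it falls short after the interviews are finished, the only remedy is to change eligibility part-way through. The power statement for n=100 would then refer to a sample that was not obtained.

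The second is overlap. The core model features include BenCGM, BurCGM, SEDM and PAID-Peds, which the article collects in the substudy 2 interview and does not list in the substudy 1 extraction. The psychosocial part of the model must therefore be learned from these interviewees. A child used for training with the label subuser can receive a baseline score pulled towards that label. Scores computed later from fresh answers are not pulled in the same way. In an arm without a control, some fall in the score could appear with no effect of the intervention.

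**Working it through.** **The protocol's 240.** With 8 predictors, 10 events per variable and 50% prevalence, N = 8 × 10 / 0.5 = 160. At 240 there are 240 × 0.5 / 8 = 15 events per variable. So 240 meets the stated condition but is not its minimum, and the derivation takes no account of the 100 subusers needed later. The n=100 cannot be reproduced, because no effect size or SD is given.

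**Inputs for supply.** Interviews: 240 (Table 1; Substudy 2, Sample Size). Subuser share p: about 0.50, the complement of the optimizer prevalence. Target: 100. Uptake u is not given; 70% to 100% is assumed.

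**Expected supply and uptake needed.** 240 × 0.50 = 120, and 100/120 = 83.3%. The pool therefore tolerates about 17% refusal or ineligibility. With full uptake, the share at which exactly 100 are expected is 100/240 = 41.7%.

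**Chance of reaching 100.** P(X ≥ 100), with X ~ Binomial(240, p × u):

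| Subuser share p | Expected subusers | u = 100% | u = 90% | u = 80% | u = 70% |
|---|---|---|---|---|---|
| 50% | 120 | 0.996 | 0.865 | 0.321 | 0.019 |
| 45% | 108 | 0.865 | 0.380 | 0.040 | <0.001 |
| 40% | 96 | 0.321 | 0.040 | 0.001 | <0.001 |
| 35% | 84 | 0.019 | <0.001 | <0.001 | <0.001 |
| 30% | 72 | <0.001 | <0.001 | <0.001 | <0.001 |

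**Interviews needed for a 90% chance of 100 enrolled** (same binomial model). At p = 50%: 218 with full uptake, 275 at 80% and 316 at 70%. At p = 30%: 370, 464 and 531.

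**What a shortfall costs.** For a two-sided paired t test at 5% with 80% power, the detectable standardized change is 0.28 SD at n=100, 0.33 SD at n=72 and 0.37 SD at n=60. Precision is lost gradually.

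**Overlap.** Substudies 1 and 2 are combined for model development, and every single-arm child comes from substudy 2. All are therefore in the development dataset. If the 80/20 split falls evenly across them, about 80 of 100 are in the training part.

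**The case against.** A reader might infer that substudy 2 cannot supply 100 subusers at all if they are a minority. The documents do not support that. Any share below 50% is a minority, and with full uptake the chance of reaching 100 is 0.98 at 48% and 0.57 at 42%. The expected minority also carries no figure and refers to month 3 in the substudy 1 cohort. Substudy 2 interviews children aged 10-18 from June 2026, at least 16 months after the dispensing window closed in February 2025, and counts discontinuers as subusers. The share then may differ in either direction.

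The low probabilities at 50% depend on assumed uptake. With full uptake, 240 is enough. The substudy 2 text also calls 240 a minimum, so a larger sample is not ruled out, although Table 1 gives n=240.

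A reader might also infer that the power statement fails. It does not follow: with no effect size stated, a smaller sample cannot be shown to be inadequate. At a change of 0.5 SD, 60 children would still give 97% power.

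Nor does the overlap invalidate the component. Its outputs in Table 1 are within-person change, feasibility, acceptability and effect-size estimates. Performance in unseen children is assigned to the held-out part, temporal validation and external replication, and the RCT enrols children who have not yet received CGM. Some single-arm children may also fall in the held-out part.

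What remains is a closed source with no uptake allowance or fallback, and a repeated score outcome whose baseline may be in-sample.

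**Conclusion.** The point holds as one of feasibility and of interpreting the score, and its severity is moderate. At the protocol's own 50%, reaching 100 needs 83% of the identified subusers to enrol. It is likely at 90% uptake, about one chance in three at 80% and remote at 70%. If the true share is about 35% or less, 100 is practically out of reach from 240 whatever the uptake. These figures rest on 240 interviews, independent binomial sampling and assumed uptake.

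The overlap is certain for the development dataset as a whole and likely for most children in its training part. It bears on the risk score and its change. Adherence measured from wear and HbA1c are not affected by it. The size of any in-sample pull on the score cannot be computed from the article. The pilot RCT and its primary between-group outcome are untouched by either problem.

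**What to change.** **Source.** In the substudy 3 Design section and the Inclusion and Exclusion Criteria, allow entry for any child aged 10-18 in the substudy 1 cohort whose subuser status (under 6 days per week, or discontinued) is confirmed at screening. Substudy 2 subusers can be approached first or alongside. For scale, at a 30% share and 70% uptake, 100 / (0.30 × 0.70) = 477 children would have to be screened to expect 100. The cohort is about 1500 of all ages; the number aged 10-18 is not stated and should be checked first.

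**Alternative.** Keep the substudy 2 source, but restate n=100 as a target, give the prevalence and uptake it assumes, and report the effect detectable at the n achieved.

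**Scores.** Widening the source does not remove the overlap, because substudy 1 data also feed the model. For children in the development dataset, use out-of-fold scores at baseline or a model fitted without them. Flag these children, and report their score change separately from that of children not used in training.

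**Cost.** Children not interviewed in substudy 2 must complete the psychosocial instruments at entry, and the change needs an ethics amendment. Out-of-fold scoring needs little extra work, since nested cross-validation is already planned. It is cheapest to settle this before substudy 2 recruitment, planned for June 2026.
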